#### *Quantitative*

In order to evaluate the efficacy of the intervention in the experimental group compared to the control group, a MANCOVA will be performed. The dependent variables are anxiety, depression, pain, quality of life and fatigue, and the independent variables are the different measurement times. We will control for the following : gender, age, socioeconomic status, diagnosis, absorption, dissociation and enjoyment. We will make post-hoc comparisons to compare scores between groups and at each measurement time. They will be made with a correction covariates Bonferroni .

Correlations will be performed on variables measured during the transplant phase, to measure the immediate effects of RVH.

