### *Multiple myeloma, lymphoma and stem cell transplantation*

Multiple myeloma patients are among those most affected in terms of quality of life. This blood cancer, which affects plasma cells, subtypes of white blood cells found in bone marrow, is the second most common hematological malignancy, and is among the top ten cancer diagnoses requiring hospitalization. The cumulative time spent receiving treatment represents a significant burden for patients, and treatments have numerous adverse effects such as fatigue, nausea and weight loss. These patients are faced with stem cell transplantation after high-dose chemotherapy, a treatment that is recognized as one of the most stressful in cancer therapy, due to numerous adverse effects, including pain, and the uncertainty linked to the fear of graft failure. Studies have shown that the quality of life of these patients was greatly diminished during and immediately after autotransplantation, with a gradual improvement during the first year of follow-up. Most of them regain a better quality of life three to five years after transplantation, while others risk developing depressive and anxiety disorders in the medium to long term.

Studies report that 26% to 36% of patients with multiple myeloma report moderate to severe depressive symptoms in the first year after transplantation, and 18% of patients suffer from moderate to severe anxiety within the first 100 days after transplantation. These rates are far higher than the general population, in which the prevalence is around 5% for depressive disorders, and 3% to 6% for generalized anxiety disorders. In this context, patients with severely impaired quality of life and depression prior to stem cell transplantation are more likely to have impaired functional status after transplantation. These data indicate a major interest in improving patients' quality of life during transplantation. By offering psychosocial management involving complementary techniques aimed at improving patients' quality of life during the sensitive period of transplantation, we can aim to reduce levels of emotional distress and thus prevent psychopathological complications in transplant patients.

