Procedures activity 2: As shown in figure 2, participants will be randomly assigned in a controlled manner with a ratio of 1:1 to two conditions: RVH and a control condition (C) consisting of usual care and a waiting list. This allocation will be done by a random draw using the *Research Randomizer* program (<https://www.randomizer.org/>), which will be conducted by a person independent of the study. The first meeting will take place on arrival at the hospital, where the study presentation will take place, and the consent form will be signed. Participants will be asked to complete self-assessments at three time points: T0=pre-, session T1=accompanied, and T2=post-transplantation (1 months) and at T3=follow-up (3 months). According to studies carried out on multiple myeloma patients, T1 is conducted between D-14 and D-1 of the transplant stay.

[figure not shown]

Measurements Activity 1: We will use two questionnaires. The first assesses the participant's satisfaction through a questionnaire 19-item, which is evaluated on an Likert scale 11-level (0 = "strongly disagree" and 10 = "strongly agree" with the proposition). A questionnaire (UEQ, 24 items, 7-level Likert) will also be used to assess the six components of user experience: usability, usefulness, hedonic qualities (e.g., originality), attractiveness, sense of presence, resulting emotions. The interview grid will be based on the same items as these questionnaires, enabling participants to develop their responses.

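### The MANCOVA is meant to compare RVH with control, but the only independent variables named are the measurement times: randomised arm and arm-by-time are missing from the model

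*Protocol*

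**What the plan says.** Under Procedures activity 2, the Protocol randomises patients 1:1 to RVH or to usual care with a waiting list. Under Measurements Activity 2, the primary outcomes are changes from T0 in anxiety and pain. The questionnaires are collected at T0, T2 (1 month after transplant) and T3 (3 months).

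The Quantitative section then sets out the analysis in four steps:

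- Purpose: "In order to evaluate the efficacy of the intervention in the experimental group compared to the control group, a MANCOVA will be performed".
- Responses and factors: "The dependent variables are anxiety, depression, pain, quality of life and fatigue", and "the independent variables are the different measurement times".
- Covariates: "We will control for the following : gender, age, socioeconomic status, diagnosis, absorption, dissociation and enjoyment".
- Follow-up tests: "We will make post-hoc comparisons to compare scores between groups and at each measurement time", with a Bonferroni correction.

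Arm therefore appears in the purpose sentence and in the post-hoc step. It does not appear in the list of independent variables or in the covariate list, and no arm-by-time term is mentioned.

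**The concern.** A model whose only factor is time estimates how the average patient changes, with both arms combined. Its omnibus test can be significant when RVH does nothing, and can miss an RVH effect when the pooled average stays flat. Neither result answers the question that the section sets itself.

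For primary outcomes defined as change from T0, the matching test is arm on change, or equivalently arm-by-time when T0 is a level of time. Neither is named. The only tests that use the randomisation are labelled post hoc, and there is no arm term in the stated model from which they would follow. Read literally, comparing groups at every measurement time also includes T0, the baseline, where a difference between arms is not evidence of efficacy.

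At stake is the trial's sole stated quantitative model for the randomised comparison. An SAP that copied the sentence would inherit the fault, and one that corrected it would contradict the Protocol.

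**Working it through.** **1. Is there a figure of the plan's own to reproduce?** None belongs to this point. The sample size of 60 is used below as an input. It cannot itself be reproduced, because the effect size, software and loss rate are left blank in the sample size justification. The point concerns model specification and does not depend on that number.

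**2. Where arm appears in the Quantitative section**

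| Element | Content | Arm included? |
|---|---|---|
| Purpose | experimental v control group | yes |
| Dependent variables | five outcomes | not applicable |
| Independent variables | measurement times | no |
| Covariates | seven named | no |
| Arm-by-time term | not mentioned | no |
| Post-hoc comparisons | between groups, and by time | yes |

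The purpose and the factor list cannot both describe the same omnibus test.

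**3. What a time-only test does when RVH has no effect (illustration).** Input from the Protocol: n = 60. Assumed, since the Protocol gives no SDs or correlations: no dropout, a shift of 0.4 or 0.5 SD between T0 and one follow-up visit, common to both arms and of either sign, and within-patient correlation r of 0.4 or 0.5. The test is a two-sided paired t-test at 0.05 on one outcome.

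- SD of change = √(2(1 − r)): r = 0.4 gives √1.2 = 1.095; r = 0.5 gives 1.000.
- Noncentrality = shift × √60 / SD of change, with √60 = 7.746.

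| Shift | r | Noncentrality | P(significant) |
|---|---|---|---|
| 0.4 | 0.4 | 0.4 × 7.746 / 1.095 = 2.83 | 0.795 |
| 0.4 | 0.5 | 0.4 × 7.746 / 1.000 = 3.10 | 0.862 |
| 0.5 | 0.4 | 0.5 × 7.746 / 1.095 = 3.54 | 0.935 |
| 0.5 | 0.5 | 0.5 × 7.746 / 1.000 = 3.87 | 0.968 |

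**4. The same comparison for five outcomes jointly.** This was simulated with 30 per arm and 2,000 runs, assuming correlation 0.5 over time and 0.4 between outcomes, no dropout and no covariates. The time-only test is a one-sample Hotelling T² on the T0–T2 and T0–T3 changes with arms pooled. The arm-by-time test is a two-sample Hotelling T² on the same changes.

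| Scenario | Time-only rejects | Arm-by-time rejects |
|---|---|---|
| No common shift, no RVH effect | 0.047 | 0.046 |
| Common shift 0.3 SD, no RVH effect | 0.615 | 0.048 |
| Common shift 0.5 SD, no RVH effect | 0.987 | 0.050 |
| Common shift 0.8 SD, no RVH effect | 1.000 | 0.050 |
| RVH effect 0.8 SD, pooled average change zero | 0.046 | 0.900 |

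The time-only test responds to the pooled change. In the last row, where that change is zero, it rejects at about its nominal level despite an RVH effect of 0.8 SD. The arm-by-time test keeps its level under a common shift and responds to RVH.

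**The case against.** The strongest reply is that the section plainly intends a between-group analysis: its first sentence says so, and it plans corrected comparisons between groups. That stands. A reader might infer that the plan tests change after transplant instead of RVH, or drops the randomised comparison. The text does not support that. The fault is a contradiction between purpose and model.

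A reader might also infer that recovery is expected in both arms and would be reported as efficacy. The background does say that quality of life is "greatly diminished during and immediately after autotransplantation, with a gradual improvement during the first year of follow-up". But that describes quality of life, a secondary outcome, and gives no course for anxiety or pain. With T0 before transplant and T2 and T3 at 1 and 3 months, the net change from T0 could be a decline, little change or an improvement. Nor does the Protocol say that a pooled time effect would be read as proof that RVH works.

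The percentages for a common shift rest on assumed shifts and correlations, and the 80% to 97% range comes from one univariate paired test, not from the planned five-outcome model with covariates. They show a mechanism and do not forecast this trial.

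Finally, the paragraph has displaced words (the word for covariates has strayed into the Bonferroni sentence), and an SAP may give the full factor structure. A dropped word for group is possible but cannot be shown. Either way, the current sentence positively names the wrong factor set, which is different from leaving detail to an SAP.

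**Conclusion.** The point holds as an internal contradiction in the stated model. The MANCOVA has a between-group purpose, but its named terms omit arm and arm-by-time, so its omnibus test, read literally, concerns change over time pooled over arms. The randomised comparison survives only in the post-hoc tests.

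This conclusion rests on the text alone. Its size is illustrative: under the assumptions stated, about 80% to 97% significant time tests with no RVH effect. The general result, that a time-only test cannot separate an RVH effect from a change common to both arms, needs none of those assumptions. The sentence should be corrected before the analysis is run.

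**What to change.** Rewrite the model sentence in the Quantitative section along these lines:

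- *The model terms are randomised arm (RVH or control), time and arm-by-time.*
- *The efficacy test is the RVH-minus-control difference in change from T0 (or in the follow-up score adjusted for its T0 value), for anxiety and for pain, with a 95% confidence interval, at [T2 or T3, to be named] or over both visits.*
- *The main effect of time is descriptive and is not evidence of efficacy.*
- *Between-group tests at T0 are not used as efficacy comparisons.*

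If T0 is kept as a level of time, the efficacy contrast sits in the arm-by-time term. If change, or the follow-up score adjusted for T0, is the response, it is the arm difference at the named visit or averaged over both. The text should say which. The Protocol does not now designate a primary visit, so the sponsor must choose one, or both together, before outcome data are examined.

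The cost is a wording change to the Protocol and any SAP. It needs no extra patients, visits or measurements.

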Measurements Activity 2: At T0, we will collect sociodemographic and data clinical from patients, including age, gender, sex, occupation, marital status, socioeconomic status and clinical diagnosis. We will also assess participants' expectations in the form of the question do you have any expectations regarding the use and efficacy of RVH? . At T0, T2 and T3, we will collect data on quality of life, anxiety, pain, fatigue and depression. The FACT-BMT is a validated scale for patients undergoing bone marrow transplantation. It contains 50 items divided into 5 subscales: Physical Well-Being, Social/Family Well-Being, Emotional Well-Being, Functional Well-Being and Bone Marrow Transplant Subscale on a 5-point Likert scale ranging from 0 = not at all to 4 = very much. The *Hospital Anxiety Depression Scale* (HADS) is a scale validated in French for cancer, which assesses participants' anxiety-depression. It is made up of 14 items: 7 items determine the degree of anxiety and the other 7, the degree of depression. The score of each subscale is calculated by summing the score of each item, which varies between 0 and 3, with each subscale reaching a maximum score of 21. Fatigue will be assessed using the 10-item version of the Multidimensional Fatigue Inventory (MFI-10) adapted to cancer. It is scored on a 5-point Likert scale ranging from 1: "strongly disagree" to 5: "strongly agree". Pain is assessed using the Brief Pain Inventory (BPI). This scale consists of 8 items on a 10-point Likert scale assessing pain severity, impact of pain on daily functions, location of pain, pain medication and extent of pain relief over the past 24 hours or week. At transplantation, we will use the diary with 11-level Scales before and after each RVH procedure to assess the direct effect of the procedure on pain, anxiety, enjoyment, i.e., the ability to enjoy oneself during the intervention, absorption, i.e., the tendency to become totally involved in a perceptual and imaginative experience, dissociation, i.e., a mental separation of components of the experience and fatigue. After each intervention, the Simulator Sickness Questionnaire, a scale validated in French, assesses symptoms of cybermalaise linked to immersion in VR. It contains 16 items divided into two subscales: nausea and oculomotor, which the participant must qualify as "not at all" (score 0), "a little" (score 1), "moderately" (score 2) or "severely" (score 3). . At T3, we will collect patients' level of satisfaction through a 19-item questionnaire that is evaluated on an 11-point Likert scale (0 = "strongly disagree" and 10 = "strongly agree" with the proposal). This questionnaire has been used in other studies to assess participant satisfaction with an intervention program^37. We will collect patients' levels of expectation and satisfaction using a five-level rating scale (1 = "not at all satisfied", 5 = "very satisfied") and explanatory interviews. Satisfaction interviews will also be conducted with caregivers in the hematology departments involved. The outcome secondary will be the change from T0 to T2 and T3 in the scores FACT-BMT, MFI and HADS-D, while the main outcomes primary will be changes from T0 in the degree of anxiety, of pain, . Changes in measures of pain, anxiety, amusement, absorption, and dissociation (logbooks completed during the two-week transplant stay) will also be considered secondary outcomes. We expect to At T3, we will assess acceptability and user experience with the User Questionnaire Experience (UEQ). This validated questionnaire is composed of 24 items that are evaluated on a 7-level Likert scale. It will be used to assess the six components of user experience: usability, usefulness, hedonic qualities (e.g., originality), attractiveness, sense of presence, resulting emotions. Sample size justification: At HMR, around 100 patients a year are treated for multiple myeloma and undergo cell transplantation stem. The sample size was also determined using a power calculation to ensure a sufficient probability of detecting a statistically significant effect, if any. We used an alpha significance level of 0.05 and a power (1 - B) of 0.95. The expected effect was estimated from \_\_\_\_\_, with an effect size of \_\_\_\_\_. Based on these

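### The between-arm efficacy MANCOVA adjusts for absorption, dissociation and enjoyment, which the protocol describes only as RVH-session diary items recorded after allocation

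*Protocol*

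**What the plan says.** The purpose of the model is given in section 3, Quantitative: "In order to evaluate the efficacy of the intervention in the experimental group compared to the control group, a MANCOVA will be performed". The covariates follow: "We will control for the following : gender, age, socioeconomic status, diagnosis, absorption, dissociation and enjoyment".

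The last three covariates appear in Measurements Activity 2 as diary items: "At transplantation, we will use the diary with 11-level Scales before and after each RVH procedure to assess the direct effect of the procedure". Enjoyment is explained there as "the ability to enjoy oneself during the intervention". None of the three is among the sociodemographic and clinical data taken at T0, and none is in the repeated battery: "At T0, T2 and T3, we will collect data on quality of life, anxiety, pain, fatigue and depression".

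The same section also treats them as outcomes. It lists changes in pain, anxiety, amusement, "absorption, and dissociation (logbooks completed during the two-week transplant stay) will also be considered secondary outcomes". Amusement appears to be the enjoyment item under another name.

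Procedures activity 2 describes the comparator as "a control condition (C) consisting of usual care and a waiting list". It mentions no RVH session and no diary for that arm. Section 2 (Objectives) and the RVH intervention text in section 3 present greater absorption as something the program is meant to bring about.

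**The concern.** A covariate in a randomised comparison should be fixed before allocation, or at least be beyond the reach of treatment. Gender, age, socioeconomic status and diagnosis qualify. Absorption, dissociation and enjoyment, as the protocol describes them, do not. They are tied to RVH sessions, which can only follow allocation. The protocol counts their changes as outcomes, and it names one of them, absorption, as an aim of the intervention.

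This MANCOVA is the only between-arm efficacy test the protocol specifies, and it covers anxiety and pain, the primary outcomes. Depending on who keeps the diary, the model either has no control patients with covariate values, or it compares the arms at equal levels of variables that RVH may itself have changed. Neither gives the total effect of being assigned to RVH.

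**Working it through.** **Step 1. Where each covariate comes from.**

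| Covariate | Described source | Before allocation? | Described for controls? |
|---|---|---|---|
| Gender, age, socioeconomic status, diagnosis | T0 data | Patient characteristics that treatment cannot change | Yes |
| Absorption, dissociation, enjoyment | Diary around each RVH session | No | No |

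**Step 2. If only the RVH arm keeps the diary.** The protocol gives 60 patients at 1:1, so about 30 per arm. Complete cases are 0 control and 30 RVH. Take a model with an intercept, an arm indicator and one diary covariate. Among complete cases the arm indicator equals 1 for everyone and duplicates the intercept. A numerical check of this design matrix gave rank 2 for 3 columns, so the arm effect is not estimable.

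**Step 3. If both arms keep a diary.** The size of the problem then depends on two quantities the protocol does not give: how far RVH shifts the covariate (s, in SDs), and what share p of the RVH effect passes through it. Both are assumptions here.

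The total effect is also an assumption, because the protocol leaves its effect size blank and the stated 60 cannot be reproduced. Working back from 30 per arm, two-sided alpha 0.05, power 0.95 and no dropout:

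d = (1.960 + 1.645) × √(2/30) = 3.605 × 0.258 ≈ 0.93 SD.

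The model was Y = (1 − p)·0.93·arm + b·M + error, with M = s·arm + noise of SD 1, b = p·0.93/s, and the error scaled so that the within-arm SD of Y is 1. The adjusted arm coefficient then targets (1 − p) × 0.93. Its standard error is about √(1 − b²) × √(2/30 + s²/58), against √(2/30) = 0.258 without M.

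Example with s = 1 and p = 0.5: b = 0.465, √(1 − 0.216) = 0.885, and √(0.0667 + 0.0172) = 0.290. The standard error is 0.885 × 0.290 ≈ 0.256, for a target of 0.465. The ratio is about 1.8, below the critical value of about 2.0, so power is under one half.

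Simulation (60 patients, 4,000 runs per scenario):

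| Share mediated | Adjusted estimate, s = 1 | Power, s = 1 | Power, s = 1.5 | Power, s = 2 |
|---|---|---|---|---|
| 0% | 0.92 | 0.87 | 0.79 | 0.69 |
| 25% | 0.70 | 0.67 | 0.56 | 0.45 |
| 50% | 0.46 | 0.41 | 0.32 | 0.25 |
| 75% | 0.23 | 0.20 | 0.12 | 0.09 |
| 100% | 0.00 | 0.05 | 0.05 | 0.05 |

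Without the covariate, the estimate was about 0.93 and power about 0.94 throughout.

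With no mediation the estimate is not biased, and the loss is precision alone, because M is correlated with arm. This is a single-outcome model with one such covariate. It illustrates the direction and range of the problem and does not reproduce the planned multivariate, repeated-time analysis.

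**The case against.** Four points can fairly be made for the plan.

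- **The diary may cover both arms.** A reader might infer that the arm effect is certainly not estimable. The documents do not go that far. The sentence on logbooks names no arm, the Activity 2 figure is not shown in the text at hand, and no missing-data rule is given that would force complete-case deletion. Non-estimability is therefore conditional. If controls do keep a logbook, though, the covariates are still measured after allocation and Step 3 applies.
- **The three are not all documented mediators.** A reader might treat all of them as the route by which RVH works. Only absorption is presented as something RVH is meant to increase. Dissociation and enjoyment are not described as mechanisms. They remain session measures and named outcomes, which is reason enough not to adjust for them.
- **Absorption could be a trait.** It is worded as a tendency, and a reading before the first session precedes exposure to RVH. A trait measure taken at T0 could be a proper covariate. None is planned, the protocol does not say which diary reading enters the model, and a pre-session reading is still described only for patients who go on to have RVH. The argument cannot reach enjoyment, which is defined by reference to the intervention.
- **The loss may be small.** A reader might conclude that the RVH effect is adjusted away. That is the extreme of an assumed range. With no mediation and a 1 SD shift, power falls only from about 0.94 to 0.87.

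These points limit how strongly the problem can be put. None of them makes the three variables suitable covariates, and no other part of the protocol resolves the matter.

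**Conclusion.** The covariate list is wrong as written. The protocol itself fixes it, so it is not a detail left to an analysis plan. The between-arm model adjusts for three variables whose only described source is the RVH-session diary and whose changes are also secondary outcomes.

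The consequence takes one of two forms. If controls have no diary and the analysis uses complete cases, about 30 of 60 patients drop out and no randomised comparison remains. If controls have a diary, the model estimates something other than the total RVH effect. The attenuation then cannot be sized from the protocol: under the stated assumptions (total effect 0.93 SD, one covariate shifted by 1 SD), it runs from none at 0% mediation to complete at 100%, with power from about 0.87 down to 0.05. No scenario examined showed a gain from the adjustment.

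**What to change.** Delete absorption, dissociation and enjoyment from the covariate list of the between-arm efficacy analysis. Keep the four listed covariates that treatment cannot affect: gender, age, socioeconomic status and diagnosis.

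State which arms complete the logbook. Analyse the three diary variables only as secondary outcomes or in a separate exploratory analysis: within the RVH arm if only that arm keeps the diary, or compared between arms if both do.

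This point does not call for adding T0 scores as covariates. They are not in the protocol's list, and T0 is already one of the assessment times, so that would be a separate change to the model.

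The cost is a short edit to the covariate list and a statement of who keeps the logbook. No new data are needed and no diary information is lost.

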
parameters, the power calculation suggests that a sample size of 60 participants is required to detect this effect with adequate power. The software \_\_\_\_ was used to perform this calculation. The sample size also takes into account a potential loss rate of \_\_\_\_%, to compensate for drop-outs and missing participants. .

Analyses Activity 1: The scores obtained on the questionnaire items will be compared with the theoretical mean of 6, i.e. the neutral level of acceptability on a scale from 0 to 10. An average above this threshold will be interpreted as a good experience of RVH. Analysis of the interview verbatim will enable us to make an open-ended assessment of the RVH experience. Significant narratives in each theme will be used to illustrate participants' opinions and experiences. Qualitative analysis of the narratives will enable us to identify positive and negative aspects, as well as avenues for improving the program. NVIVO software will be used for these analyses. This study will enable relevant modifications to be made to the program prior to the clinical effects study.

Analysis activity 2 :

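### Anxiety and pain are primary, but no primary visit is named and their only planned test pools them with three secondary outcomes under a Bonferroni correction of unstated scope

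*Protocol*

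**What the plan says.** Protocol section 3, Measurements Activity 2, sets the hierarchy of outcomes. For the primaries it reads "the main outcomes primary will be changes from T0 in the degree of anxiety, of pain", with no visit attached and no statement of whether one or both must succeed. For the secondaries it does give visits: "The outcome secondary will be the change from T0 to T2 and T3 in the scores FACT-BMT, MFI and HADS-D". The same paragraph has quality of life, anxiety, pain, fatigue and depression all collected at T0, T2 and T3.

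The Quantitative subsection under Analysis activity 2 does not carry the hierarchy over. It plans one MANCOVA with anxiety, depression, pain, quality of life and fatigue as dependent variables. It continues: "We will make post-hoc comparisons to compare scores between groups and at each measurement time". On multiplicity it says only "They will be made with a correction covariates Bonferroni".

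The sample size paragraph works at one significance level: "We used an alpha significance level of 0.05 and a power (1 - B) of 0.95". The effect size, its source, the software and the loss rate are left blank, and no allowance for several tests is stated.

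**The concern.** A primary outcome needs a measure, a time point and a test. Here the time point is missing, and the test is shared with outcomes that the protocol itself ranks as secondary. Three consequences follow.

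- A difference in depression or fatigue alone can make the five-outcome MANCOVA significant, so that result does not answer whether anxiety or pain improved.
- Anxiety and pain are examined by themselves only in the post-hoc comparisons, and their significance level depends on a Bonferroni family that the protocol does not define. A wide family spends alpha on secondary outcomes. A narrow one leaves two outcomes at two visits, any of which could be presented as the primary result.
- Read literally, comparing groups at each measurement time includes T0. Under randomisation any baseline difference is due to chance, so that test says nothing about the intervention.

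At stake is whether a positive result could be tied to a contrast fixed in advance.

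**Working it through.** **Inputs from the protocol.** Alpha 0.05 and power 0.95; "sample size of 60 participants is required to detect this effect with adequate power"; allocation "with a ratio of 1:1 to two conditions", so 30 per arm; five outcomes; collection at T0, T2 and T3. Assumed: two-sided testing, because sidedness is not stated.

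**The plan's own figure.** The 60 cannot be reproduced, because the effect size is blank (the text breaks off after "The expected effect was estimated from"). It can only be inverted. By the normal approximation, d = (1.960 + 1.645) × √(2/30) = 0.93. By the noncentral t with 58 degrees of freedom, d = 0.947. I use 0.947 as a working assumption, not as the sponsor's value.

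**Size of the Bonferroni family.** The text allows several readings:

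- all outcomes, all times: 5 × 3 = 15 tests, 0.05/15 = 0.0033 each
- all outcomes, T2 and T3 only: 5 × 2 = 10 tests, 0.05/10 = 0.005 each
- within each outcome, three times: 0.05/3 = 0.0167 each
- within each outcome, T2 and T3: 0.05/2 = 0.025 each

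**Power per primary test.** This is the noncentral t with 30 per arm and noncentrality d × √(30/2) = 0.947 × 3.873 = 3.67, compared with the two-sided critical value on 58 degrees of freedom.

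| Tests in family | Alpha per test | Critical t | Power at d = 0.947 | Power at d = 0.8 |
|---|---|---|---|---|
| 1 | 0.05 | 2.00 | 95% | 86% |
| 2 | 0.025 | 2.30 | 91% | 79% |
| 3 | 0.0167 | 2.47 | 88% | 74% |
| 10 | 0.005 | 2.92 | 77% | 57% |
| 15 | 0.0033 | 3.06 | 72% | 52% |

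The last column shows how the loss grows if the true effect is smaller; 0.8 is also an assumption. All figures ignore covariate adjustment.

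**Family-wise error over the two primaries at T2 and T3 (four tests, taken as independent).**

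- Corrected within each outcome for two visits: 1 − (1 − 0.025)⁴ = 9.6%.
- Corrected within each outcome for three times: 1 − (1 − 0.0167)⁴ = 6.5%.
- Corrected over 10 or 15 tests: at most 5%, by construction.

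Positive correlation between the scales and visits would bring the first two figures down.

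**The case against.** The strongest reply is that Bonferroni is planned, and that its family and any test hierarchy are commonly left to a statistical analysis plan, which is not shown here. That holds for the family size, which is why the consequence can only be given as a range. It does not cover the rest: the protocol itself omits the primary visit where it gives the secondary visits, and it specifies an analysis that ignores its own ranking. The primary sentence is visibly damaged and words may have been lost, but no other part of the protocol supplies the visit.

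Stronger conclusions that a reader might draw do not stand:

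- *Family-wise error of 18.5%.* This is 1 − 0.95⁴, which requires no correction at all. The protocol announces one.
- *Fifteen tests as the plan.* This is one reading only. The outcomes are changes from T0, which do not exist at T0, so ten is the more natural count, and correction within each outcome fits the text equally well.
- *A further fall in power from drop-out.* The sample size paragraph says that 60 already allows for loss, at a blank rate. Removing patients from a d that was solved for 60 completers would count the loss twice.
- *No error control at all.* Bonferroni over every test does control error and costs only power. The two harms are alternatives and do not add up.
- *The MANCOVA as a formal gate.* The protocol does not say that it must be significant before the comparisons are made.

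**Conclusion.** The point holds. The protocol names no visit for its primary outcomes, and its stated analysis does not isolate them from three secondary ones. The size depends on a choice that the protocol leaves open. Under a family spanning all outcomes, power per primary test falls from 95% to 77%, at worst 72%, with error controlled. Under correction within each outcome, power stays at 88% to 91%, but family-wise error over the primaries is about 6.5% to 9.6%. These figures rest on the back-solved d = 0.947, two-sided tests, 30 analysed per arm and, for the error rates, independence. The structural defect does not depend on any of these assumptions.

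**What to change.** Before any results are seen:

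1. Name one primary visit and one score each for anxiety (the HADS anxiety subscale) and pain (a specified BPI score). The choice of visit and BPI score belongs to the investigators; the text does not favour one.
2. Make the two RVH-minus-control contrasts in change from T0 at that visit the only primary family, tested with Holm (the smaller p-value at 0.025, then the other at 0.05). Power at the first step is about 91% under the same assumption.
3. Report the other visit, FACT-BMT, MFI and HADS-D as secondary estimates with 95% confidence intervals.
4. Do not rest the efficacy conclusion on the five-outcome MANCOVA, and drop between-group tests at T0.
5. State the sample size at the alpha that results, with the blank effect size filled in.

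The cost is protocol wording. The other visit and the three secondary scales lose any confirmatory claim.
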